#### Missing data and dropout

3.10.3

We anticipate approximately 15% of the original 240 participants will drop out by week 26. The primary analysis of Aim 1 will be all available data, which may include some intermittent missingness, and some dropout. Because we cannot determine the cause of missingness, we will follow the primary analysis with a sensitivity analysis, looking for evidence of bias in our estimates revealed by the application of various data models. Those models will include (1) completers only, (2) last observation carried forward, (3) missing equals return to baseline smoking, and (4) multiple imputation using the MICE method.

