**Fig. 1 fig1:**
[figure not shown]
Overview of study design.

Participants will then receive instructions and an action plan to switch to e-cigarettes for the following 6 weeks (weeks 2-7). Participants will collect their used cigarette filters and their used e-cigarette pods daily to assess consumption of cigarettes per day (CPD) and pods per day (PPD). The primary outcome will be the longitudinal daily count of cigarettes from baseline to the end of the 6-week e-cigarette switch phase. A secondary endpoint will be cigarettes per day from week 8 to week 26, measured by timeline-follow-back (TLFB). Complete switching will be verified with a carbon monoxide (CO) value < 5 ppm. Secondary outcomes include subjective reward, relative reinforcing value, and positive affect. The protocol was approved by the University of Pennsylvania's Institutional Review Board (854051) and participants provided written informed consent.

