#### Action plan

3.6.2

Participants will receive a six-week supply of e-cigarettes, distributed weekly, according to their flavor assignment. Before beginning the switch phase, participants will meet with a research staff member to receive instructions on how and when to use the e-cigarette and to develop an action plan for switching [8,14]. The 30-min action plan will include preparing for switch day, managing smoking triggers, and garnering support for behavior change. Studies have shown that brief preparation for switching from combustible to e-cigarettes is associated with higher smoking abstinence rates at 8 weeks and greater reductions in harmful chemical exposure than participants not receiving instructions [8,14], even among smokers uninterested in quitting smoking immediately [8]. As such, the action plan enables all participants to begin with the same level of preparation while maximizing external validity.

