### Follow-up (Weeks 8-26)

3.7

The switch phase will conclude at the end of week 7. Participants will then receive information on where and how to buy common e-cigarette brands, with attention to nicotine content [43]. Details on open and closed e-liquid systems, including disposables and potential purchase locations, will also be provided [44]. While non-disposable menthol and tobacco-flavored pod-style e-cigarettes are widely available, fruit-flavored pod-style e-cigarettes are less accessible. Up to 39% of brick-and-mortar stores continue to sell them, and online stores remain a possible source [45]. Disposable fruit-flavored pod-style e-cigarettes are easily found in vape shops throughout the city area, as are open e-cigarette systems that allow adding fruit-flavored e-liquid.

Participants will complete an in-person follow-up at 26 weeks. This follow-up will allow an assessment of cigarette smoking behavior, ongoing e-cigarette use [14], and the characteristics of e-cigarette use (such as device type, flavor, quantity of use, and nicotine content). This will enable us to observe short-term and long-term sustained switching, delayed switching, shifts in dual use, and the return to exclusive smoking [46] as participants navigate the current and evolving tobacco marketplace.

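### At week 26 the LOCF sensitivity model can only carry forward counts from day 49 or earlier, so it assumes the persistence that week 26 is meant to test (cheap improvement, secondary endpoint)

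*Protocol article*

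**What the plan says.** Section 3.10.3 sets the main approach: "The primary analysis of Aim 1 will be all available data, which may include some intermittent missingness, and some dropout". It says that the cause of missingness cannot be determined and that sensitivity models will be run to look for bias. They are listed as "1) completers only, (2) last observation carried forward, (3) missing equals return to baseline smoking, and (4) multiple imputation using the MICE method", with no ranking and no distinction between the six-week and week-26 endpoints. On the amount of loss it says: "We anticipate approximately 15% of the original 240 participants will drop out by week 26". Neither the timing of dropout nor its split by arm is given.

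The supply is limited in time. Section 3.6.2 states: "Participants will receive a six-week supply of e-cigarettes, distributed weekly, according to their flavor assignment". Section 3.7 adds: "The switch phase will conclude at the end of week 7". During days 8–49 smoking is measured by daily counts of returned filters (Sections 3.6.3 and 3.8).

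After that there is one contact: "Participants will complete an in-person follow-up at 26 weeks" (Section 3.7). Smoking over weeks 8–26 is recalled then by timeline follow-back (Sections 3.1 and 3.8). Section 3.7 gives the purpose as observing "short-term and long-term sustained switching, delayed switching, shifts in dual use, and the return to exclusive smoking". It notes that fruit-flavored pods are harder to get than menthol or tobacco pods. It also says that disposable fruit products and open systems are easy to find.

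**The concern.** Week 26 is there to show whether switching lasts once the supplied product stops. A participant lost after day 49 has no smoking data from that period. LOCF fills the gap with a filter count taken while the assigned flavor was free and filter collection was paid, and treats it as equivalent to a week-26 recall average. That builds in the answer: no change after supply ends.

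If the fruit-versus-comparator gap narrows after day 49 among those lost, LOCF reports a larger week-26 gap than the true one. The other listed models leave part of the question open. All-available-data, completers-only and MICE rest on broadly similar assumptions that dropout is ignorable. Return-to-baseline departs from them, but at a single extreme and identically in every arm. Partial relapse, or relapse that differs by flavor, is not examined by any of the listed models. At stake is how far the sensitivity analysis can test a claim of sustained switching.

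**Working it through.** **1. No assessment between day 49 and week 26.** Section 3.1 gives nine visits. Days 6, 7, 14, 21, 28, 35, 42 and 49 and week 26 make nine, with intake counted separately. Table 1 has no column between weeks 2–7 and week 26. So for anyone missing week 26, the last observation dates from day 49 or earlier.

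**2. Inputs.**
- Dropout p = 0.15 (Section 3.10.3); 0.15 × 240 = 36 people.
- Detectable difference about 3.73 cigarettes per day (CPD), 70 per group, two-sided alpha 2.5%, power 80%, and SD of change 7.1 (Section 3.10.1).
- Assumed: all dropout after day 49; equal by arm unless stated; a switch-phase gap of 3.73, from illustrative reductions of 9.73 (fruit) and 6.00 (comparator).

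**3. The plan's own figure.** With 70 per arm, the noncentral t gives 0.526 SD, and 0.526 × 7.1 = 3.73 CPD. The normal approximation gives 0.521 × 7.1 = 3.70. The stated 3.73 is reproduced. It is a detectable difference, not a forecast.

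**4. LOCF excess, equal dropout.** Completers contribute their observed week-26 value to both LOCF and the truth, so they cancel:

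excess = p × (switch-phase gap − true week-26 gap among dropouts) = 0.15 × (3.73 − g)

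| True gap g among dropouts | Excess (CPD) |
|---|---|
| 0 | 0.56 |
| 1 | 0.41 |
| 2 | 0.26 |
| 3.73 | 0 |

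The 0.56 is 15% of 3.73. If the true gap is zero in everyone, a test with 80 per arm and SD 7.1 rejects in favor of fruit about 4% of the time under LOCF, against a nominal 1.25%.

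**5. The models side by side.** Fruit advantage in CPD at week 26, with 15% lost per arm and dropouts truly back at baseline. MICE is approximated as dropouts resembling completers.

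| Completers' week-26 gap | Truth | Completers-only, MICE | LOCF | Return to baseline |
|---|---|---|---|---|
| 3.73 | 3.17 | 3.73 | 3.73 | 3.17 |
| 1.50 | 1.27 | 1.50 | 1.83 | 1.27 |
| 0 | 0 | 0 | 0.56 | 0 |

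Middle row: truth 0.85 × 1.50 = 1.27 (1.275 before rounding); LOCF 1.275 + 0.15 × 3.73 = 1.83.

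**6. Unequal dropout.** Completers in both arms reduce by 5, and dropouts are back at baseline.
- 25% lost in fruit, 10% in the comparator: truth 0.75 × 5 − 0.90 × 5 = −0.75. LOCF (3.75 + 0.25 × 9.73) − (4.50 + 0.10 × 6.00) = 6.18 − 5.10 = +1.08.
- 10% in fruit, 20% in the comparator: truth 4.50 − 4.00 = 0.50. LOCF (4.50 + 0.973) − (4.00 + 1.20) = 0.27, an understatement.

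**7. What one common extreme leaves out.** Let completers keep the 3.73 gap and let dropouts go a fraction s of the way back to baseline in both arms. The gap is 3.73 × (1 − 0.15s): 3.73, 3.59, 3.45, 3.31 and 3.17 for s = 0, 25%, 50%, 75% and 100%. If only fruit dropouts relapse fully, it is 0.85 × 9.73 − 6.00 = 2.27. That is below the 3.17 from return-to-baseline, so that model is not the least favorable case for fruit.

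**The case against.** A reader might infer three stronger things, and the documents support none of them.

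- *LOCF scores everyone lost after day 49 as a sustained switcher.* It carries whatever was last seen. Someone still smoking is scored as smoking, and someone lost before day 8 carries a baseline count. If dropouts were already back at baseline level by day 49, LOCF equals return-to-baseline. With no switch-phase gap and equal dropout, LOCF does not bias the difference.
- *LOCF, completers-only and MICE together would make an overstated fruit advantage look robust.* In the comparison above they agree only when completers keep the full gap. There LOCF adds no error beyond the primary analysis, and return-to-baseline shows 3.17. When the effect fades, completers-only and MICE disagree with LOCF (0 against 0.56). The plan does not tell anyone to count agreeing models or discount return-to-baseline.
- *Section 3.7 predicts relapse, especially in the fruit arm.* It lists return to smoking as one of several outcomes to observe, and says that other fruit products are easy to find.

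It can also be said that delta steps and tipping points usually belong in an analysis plan, which is not shown, and that the list of models is worded as open-ended. That stands: their absence here is not an error. What remains is that the protocol itself names LOCF and does not exempt week 26.

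The calculation is also an upper-end illustration. It puts all dropout after day 49 and works in raw CPD, whereas Section 3.10.2 analyzes percent of baseline. The same identity holds on that scale, but the figure in CPD does not transfer.

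**Conclusion.** The point holds as a cheap improvement of low severity. LOCF is a poor model for week 26 because the visit schedule leaves it nothing from after supply ended to carry forward. Under equal dropout, all after day 49, and a 3.73 CPD switch-phase gap, its excess runs from 0 to 0.56 CPD as the true gap among dropouts runs from 3.73 to zero. Unequal dropout can enlarge, shrink or reverse the bias. All-available-data, completers-only and MICE do not share this error, though their assumptions about dropout are similar to one another. Return-to-baseline is a useful check already in the plan, limited to full relapse applied alike in every arm. The matter touches one of four unranked sensitivity models on a secondary endpoint. Nothing is claimed about the six-week primary endpoint.

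**What to change.** In Section 3.10.3, for the week-26 endpoint:

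- Drop LOCF and put delta-adjusted multiple imputation in its place. Run the planned MICE by arm, then move imputed post-dropout smoking 0%, 25%, 50%, 75% and 100% of the way back to each person's baseline.
- Let the shift differ between fruit and each comparator, and report the tipping point at which the fruit-versus-tobacco and fruit-versus-menthol conclusions change.
- Keep all-available data as primary and return-to-baseline as the 100% end of the scale.
- Report dropout by arm, and state that agreement between the primary, completers-only and MICE results is not evidence against informative dropout.

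The cost is a wording change and a little more programming on an imputation already planned, with no new data, visits or participants. The downside is that the week-26 conclusion may look less robust.

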## Discussion

4

Despite the public health and regulatory significance, the field has little understanding of the effects of e-cigarette flavoring on the likelihood of switching from combustible cigarettes to e-cigarettes. Such information is critical, as the availability of e-cigarette flavoring in the marketplace has been the subject of vigorous debate [19,71]. Converging lines of research provide a strong scientific premise for a prospective investigation of the role of fruit flavor in the substitutability of e-cigarettes for combustible cigarettes among adults who have been unable to quit smoking with traditional approaches. This protocol describes the first randomized clinical trial to assess the effects of e-cigarette flavoring on switching from combustible cigarettes to e-cigarettes, and the likely mechanisms driving initial and sustained switching.

This clinical trial features several well-reasoned and innovative design choices. For example, the hedonic and motivational mechanisms that are key indicators of abuse liability, namely subjective rewarding value and relative reinforcing value, are likely the same mechanisms that explain a noncombustible nicotine delivery product's ability to fully substitute for combustible cigarettes. As the influx of alternative nicotine delivery products in the marketplace continues, these variables could serve as an early indicator of their value as a cessation aid. These indices will be examined in the laboratory using well-validated behavioral choice paradigms [23,34], and then mapped onto cigarette smoking behavior in a real-world setting. Thus, both laboratory and field methods are used to address public health and policy-relevant research questions regarding e-cigarette flavoring. Additionally, we will evaluate whether the rewarding and positively reinforcing effects of fruit versus traditional flavoring drive switching behavior, while accounting for negative reinforcing effects, such as reduced craving, withdrawal, and negative affect.

The study focuses on AWS who have tried repeatedly, but unsuccessfully, to quit smoking. While this may lessen generalizability, this population is most suited to a harm-reduction approach [7,16,19]. These AWS have not been successful with medication and their likelihood of quitting is less when the same medication is used on sequential attempts [72]. With only three medications approved by the FDA over the past five decades, these individuals have few options. Research indicates adults are turning to e-cigarettes more frequently than any other medicinal smoking cessation product [73].

If the hypotheses are supported, it would suggest that the unavailability of fruit-flavoring in e-cigarettes would unintentionally support continued combustible cigarette smoking among adults who have not been able to quit using traditional approaches. The findings may help to catalyze thinking surrounding the need for regulatory precision (e.g., moving all non-medicinal nicotine to adult retail outlets) rather than a complete flavor ban [19,71,74] to protect youth from using e-cigarettes while promoting use among smokers unable to quit smoking otherwise. If the hypotheses were not supported, it would suggest that fruit-flavored e-cigarettes do not confer an advantage over traditional flavors for smoking cessation and that their absence from the market does not negatively affect AWS who want to quit through e-cigarette use.

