## Aims and hypotheses

2

The current study (NCT06264154) has two aims. Aim 1 seeks to evaluate the effects of fruit-flavored versus tobacco-flavored and menthol-flavored e-cigarettes on combustible cigarette smoking among adults who have persistently smoked. We hypothesize that participants randomized to fruit-flavored e-cigarettes will be more likely to switch from combustible cigarettes to e-cigarettes during the 6-week switch phase and at the 26-week follow-up than participants randomized to tobacco-flavored or menthol-flavored e-cigarettes. Complete switching, partial switching, and no switching will be measured. Aim 2 seeks to examine whether the rewarding and reinforcing effects of e-cigarette flavoring mediate switching behavior. We hypothesize that fruit-flavored e-cigarettes will produce greater subjective reward, relative reinforcing value, and positive affect than tobacco-flavored or menthol-flavored e-cigarettes. In turn, greater subjective reward, relative reinforcing value, and positive affect will predict fewer cigarettes smoked per day during the 6-week switch phase and at the 26-week follow-up.

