### Overview of study design

3.1

The proposed study will evaluate whether fruit-flavored (FF: watermelon and blueberry) versus traditional-flavored e-cigarettes [tobacco (TF) or menthol (MF)] more readily substitute for combustible cigarettes and if the rewarding and reinforcing effects of flavoring facilitate changes in smoking behavior among 210 adults who have persistently smoked cigarettes. Eligible adults will be randomly assigned 1:1:1 to FF (n = 70), TF (n = 70), or MF (n = 70) and participate in 9 visits across 26 weeks (see Fig. 1). Baseline cigarette smoking rate will be established over days 1-5. After overnight smoking abstinence, a laboratory visit on day 6 will assess e-cigarette flavor-associated subjective reward, affect, craving relief, and withdrawal relief. After overnight smoking abstinence, a laboratory visit on day 7 will assess the reinforcing value of the assigned e-cigarette flavor relative to combustible cigarettes.

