#### Sample size

3.10.1

For Aim 1, hypotheses will be tested with 80% power using 5% two-sided alpha Bonferroni corrected to 2.5% for two group comparisons. The primary outcome is the longitudinal daily cigarette count from baseline (days 1-5) to the end of the e-cigarette switch phase (day 49), with week 26 as a secondary endpoint. We based the power on data from prior switching studies. A sample of 210 (70 per group) will allow us to detect an overall standardized slope of 0.19. To account for a ∼15% attrition rate [67], we will enroll ∼ 240 participants to have 210 who complete the 26-week follow-up. We expect the initial and sustained switch for participants randomized to fruit-flavoring to be greater than for participants randomized to tobacco or menthol flavoring. A sample of 70 per group enables us to detect a difference of ∼3.73 cigarettes per day (CPD). We will also be able to detect a difference in slopes of 0.13 (CPD per day change).

For Aim 2, a sample of 70 per group will allow us to detect a between-group effect size of 0.5. For the relative reinforcing value of flavored e-cigarettes (RRVF), this means we can detect a difference in breakpoint of 2.0. Positive affect will be assessed as a difference score with a standard deviation of approximately 7.0, yielding 80% power to detect a difference of approximately 3.7. Subjective reward has a standard deviation of 1.3, which allows us to detect a 0.68 difference. In turn, the continuous measures of RRVF, positive affect, and subjective reward will be used to predict changes in mean cigarette counts from baseline to the end of the switch phase and from baseline to the 26-week follow-up. The sample of 210 allows us to detect a standardized slope of 0.2. The actual standard deviation for the cigarette consumption change score is 7.1. The detectable slopes are 0.37 for RRVF, 0.20 for positive affect, and 1.07 for subjective reward.

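### The Discussion would read unsupported superiority hypotheses as suggesting no advantage of fruit flavors and no effect of their market absence, which this design cannot support

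*Protocol article*

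**What the plan says.** Section 4 (Discussion) sets out what each outcome of the trial would mean. For the negative outcome it says: "If the hypotheses were not supported, it would suggest that fruit-flavored e-cigarettes do not confer an advantage over traditional flavors for smoking cessation". The sentence goes on to infer that "their absence from the market does not negatively affect AWS who want to quit through e-cigarette use".

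The hypotheses behind this are directional. Section 2 (Aims and hypotheses) expects that "participants randomized to fruit-flavored e-cigarettes will be more likely to switch from combustible cigarettes to e-cigarettes during the 6-week switch phase", compared with the tobacco and menthol groups, and likewise at 26 weeks. Section 3.10.2 (Data analysis) tests this through the interaction of study phase and flavor group in a mixed model, with fruit as the reference. That is a test of difference.

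Section 3.10.1 (Sample size) states that "hypotheses will be tested with 80% power using 5% two-sided alpha Bonferroni corrected to 2.5% for two group comparisons". It gives a detectable difference of about 3.73 CPD with 70 per group, together with detectable slopes. The article names no equivalence or non-inferiority margin and no smallest important benefit.

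**The concern.** A test of superiority that fails to reject has two possible explanations: there is no benefit worth having, or there is one and the trial did not detect it. Only the confidence interval, set against a benefit judged to matter, can separate the two. The Discussion sentence goes straight from unsupported hypotheses to the first explanation.

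The stakes lie in how the result will be used. The Discussion presents the trial as policy-relevant and refers to a flavor ban. After a non-significant result, this sentence would support saying that removing fruit flavors costs smokers nothing, when the data might still be compatible with a benefit of several cigarettes per day.

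The second half of the sentence goes further still. The trial randomizes the flavor supplied for six weeks. It does not randomize whether fruit flavors can be bought.

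**Working it through.** **Inputs.** Arms: "Eligible adults will be randomly assigned 1:1:1 to FF (n = 70), TF (n = 70), or MF (n = 70"). Alpha is 2.5% two-sided per comparison and power 80% (section 3.10.1). For the SD, the Aim 2 paragraph of the same section says: "The actual standard deviation for the cigarette consumption change score is 7.1". Using that SD for Aim 1 is an assumption, which step 1 checks.

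**1. Reproduce the plan's figure.** The standard error of a difference between two arms is 7.1 × √(2/70) = 1.20 CPD.
- Normal approximation: (2.241 + 0.842) × 1.20 = 3.70 CPD.
- Noncentral t, 138 degrees of freedom: 3.73 CPD, as stated.
- At alpha 5% the result would be 3.36 (normal) or 3.39 (t), which does not match.

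So SD 7.1 with alpha 2.5% reproduces the stated 3.73.

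**2. What a non-significant result leaves open.** The half-width of the 97.5% interval is 2.266 × 1.20 = 2.72 CPD.
- Observed difference 0: a benefit of up to 2.72 CPD remains compatible with the data.
- Observed 1.0: up to 1.0 + 2.72 = 3.72.
- Observed 2.6 (still non-significant, since 2.6 < 2.72): up to 5.32.
- The detectable difference of 3.73 is excluded only if the observed difference is below 3.73 − 2.72 = 1.01 CPD.

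**3. How often a true benefit would be non-significant.** For a single comparison, the noncentral t is used with noncentrality d/1.20. For both comparisons together, two normal test statistics are used, each with mean d/1.20 and critical value 2.241. Their correlation is 0.5, because they share the fruit arm: (σ²/70)/(2σ²/70) = 0.5. An equal benefit over both comparators is assumed.

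| True benefit (CPD) | d/SE | One comparison non-significant | Both non-significant |
|---|---|---|---|
| 2.0 | 1.67 | 72% | 58% |
| 2.5 | 2.08 | 57% | 40% |
| 3.0 | 2.50 | 41% | 24% |

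The three benefits are illustrative. The article does not say which benefit would matter.

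**4. Sensitivity to the SD (assumed range 6 to 9).**
- Half-width: 2.266 × 6 × √(2/70) = 2.30 CPD, and 2.266 × 9 × √(2/70) = 3.45 CPD.
- A true benefit of 2.0 CPD is non-significant in one comparison 61% of the time with SD 6 and 83% with SD 9.

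**5. Sample size needed to exclude a benefit of size m.** With a true difference of 0, one-sided 1.25% and 80% power, n per arm = 2 × (7.1 × (2.241 + 0.842)/m)². This gives 959 for m = 1, 240 for m = 2, 107 for m = 3 and 69 for m = 3.73. With 70 per arm, the trial is sized to exclude only a benefit of about 3.7 CPD or more.

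**The case against.** The strongest reply is that the sentence is implications prose. It says the result would suggest something, not that it would show it. It mirrors an equally hedged sentence about the positive outcome, and it changes nothing in the design, the test or the data collected. All of that is right, and it limits the point. A reader might infer that the plan sets a formal decision rule equating non-significance with no effect. Sections 3.10.1 and 3.10.2 contain no such rule. The hedge, however, does not make the inference valid, and this is the only reading of a negative result that the article offers.

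Other replies stand in part:

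- **A superiority trial needs no equivalence margin, and interval reporting may be left to a fuller document.** Agreed. Neither absence is a fault here. The fault is a stated conclusion that would need both.
- **The trial is not sized on 3.73 CPD alone.** Correct: section 3.10.1 also gives an overall standardized slope of 0.19 and a slope difference of 0.13 CPD per day. These do not justify reading a null result as no advantage.
- **The hypotheses are plural.** If unsupported means that both Aim 1 comparisons fail, the single-comparison rates overstate the risk, so both columns are given. It would be too strong to say that relevant benefits would usually be missed: at 3.0 CPD the rate is 41% for one comparison and 24% for both.
- **The primary model differs from a two-sample t-test.** It is a mixed model on daily counts as a percentage of baseline, with covariates, and may be more precise. The figures are therefore approximations.

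**Conclusion.** The point holds as a correction to a stated interpretation. It is not a defect in the planned analysis. Unsupported superiority hypotheses would not, on this design, suggest that fruit flavors lack an advantage. On the plan's own inputs, even an observed difference of zero leaves a benefit of about 2.7 CPD compatible with the data. A true benefit of 2.0 CPD would be non-significant in both comparisons more often than not (58%).

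This rests on the change-score SD of 7.1 carrying over to Aim 1, on a two-sample comparison standing in for the mixed model, and, for the joint rates, on an equal benefit over tobacco and menthol. The exact percentages would move with a more precise model, but the logical gap would remain. The figures are in cigarettes per day, the measure used for the Aim 1 detectable differences, whereas the Discussion sentence speaks of smoking cessation.

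The market-absence statement fails on a separate ground, whatever the precision: availability is not what the trial randomizes.

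**What to change.** Reword the Discussion sentence in three respects:

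1. Report a non-significant result as inconclusive, with the 97.5% confidence interval for each of the two comparisons.
2. State that there is no meaningful advantage only if the interval excludes a smallest important benefit that is justified and fixed before analysis. The 3.73 CPD detectable difference should not be the default. It reflects the sample size and not a judgement of importance, and it would allow benefits just below it to be dismissed.
3. Remove the statement that market absence does no harm. Meeting a margin in cigarettes per day would not restore it.

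The cost is a few lines of wording and a weaker claim after a negative trial, with no change to design, conduct or sample size. The team should expect the rule in item 2 to be hard to meet. With a half-width of 2.72 CPD and, for illustration, a smallest important benefit of 2 CPD, the interval would exclude it only if the observed difference favored the comparator by more than 0.72 CPD (2 − 2.72 = −0.72).
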